### Outcome measures

3.9

The Working Alliance Inventory Short Questionnaire (WAI‐S), patient version. This is an instrument for measuring the working alliance, and therefore, the therapeutic relationship between professional and patient (Horvath & Greenberg, 1989). The short version of the WAI has 12 items, each item is rated by the professional and the patient on a Likert scale ranging from 1 (never) to 7 (always). This instrument is made up of three factors: bonding, agreement on objectives and agreement on tasks. The Spanish adaptation of Andrade‐González and Fernández‐Liria (2015) presents Cronbach's *α* values of 0.93 for the total scale and 0.85, 0.81 and 0.90 for each of the factors.The Quality in Psychiatric Care scale (QPC: Schröder et al., 2007) assesses the quality of care and is the best suited to evaluate the quality of care in psychiatric units. The QPC contains 30 items and each item is evaluated by means of a Likert scale with four response options, where 1 indicates total disagreement and 4 indicates total agreement. It is composed of six dimensions: therapeutic relationship, patient participation, support received, environment, safety and hospital discharge. The maximum score is 120 points, and the minimum is 30 points. A high score in each dimension or in the total scale would indicate a very good perception of quality on behalf of the patient. The Spanish version will be used (Sanchez‐Balcells et al., 2021) which presents a Cronbach's *α* of 0.94 for the total scale and for five of the six dimensions it was over 0.7, except for the dimension measuring the environment, which was 0.67.The Coercion Experience Scale (CES‐18: Bergk et al., 2010). This scale assesses the subjective experience of coercion during psychiatric hospitalization. The CES‐18 in its short version consists of 18 items that are divided into 2 dimensions, one measuring coercion and humiliation and the other fear, on a five‐point Likert‐type scale (1‐never and 5‐always); where participants rate and record their own evaluation and self‐perception of the coercive intervention experienced. This instrument was validated in a Spanish population by Aguilera‐Serrano et al. (2019), which presents a Cronbach's *α* of 0.94 for the total scale and 0.93 and 0.71 for its two factors.

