## BACKGROUND

2

In recent years, the national strategies on mental health in Catalonia and Spain have been aimed at person‐centred care and personal recovery. Thus, one of the main strategic lines of action is to improve care practices in relation to people's rights and to strengthen new capacities for the participation and empowerment of service users (Generalitat de Catalunya, Departament de Salut, 2017; Spanish Ministry of Health, 2022). In Spain, from a training point of view, one of the main challenges is to adapt the supply of training places for specialist nurses, as mental health nursing is recognized with an official postgraduate specialized training qualification (Spanish Ministry of Health, 2022). Along the same lines, the policy guidelines are committed to improving practice by promoting the active participation of professionals and users through the principles of dialogue, active listening and the person with mental health problems as a subject of rights (Generalitat de Catalunya, Departament de Salut, 2017; Spanish Ministry of Health, 2022). There is no doubt that it is through the therapeutic relationship that nurses in mental health care settings can enhance person‐centred practice (Tolosa‐Merlos et al., 2022). It is, therefore, a challenge for nurses to respond to these needs in the context of Spanish mental health inpatient units, where some users are admitted involuntarily (Wasserman et al., 2020) and remain in the hospital for an average stay of 15–16 days (Spanish Ministry of Health, 2022).

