### Recruitment and data collection

3.10

Once the centres have been randomized and the collaborating nurses of the units where the intervention will be carried out have been trained, the person from the research team coordinating the study in each unit will be responsible for informing the patients who meet the inclusion criteria between 24 and 72 h from the time of admission about the objectives of the study and will obtain informed consent. Patients will be recruited consecutively and will receive a confidential code assigned by the project coordinator, which will be their identification for the data collection dossiers. In the case of patients from centres chosen for the intervention, one of the nurses who has received the training will be assigned to the patient. In the case of control centres, the usual process of assigning a nurse from the unit will be followed and the nurse will not have any notification in this regard. In both cases, once the first meeting or welcome interview by the referring nurse in the unit has taken place, the baseline assessment (T1) will be carried out by a nurse who is not involved in the patient's care process and who has been previously trained in the measurement instruments. The baseline assessment will be included in the T1 dossier and will consist of administering the WAI‐S and QPQ instruments. Prior to discharge, the same person outside the care process of the hospitalized person will administer the instruments to the user for the follow‐up assessment included in the T2 dossier, which will include the WAI‐S, the QPC and the CES (T2). The remaining data will be obtained from the patient's clinical history and will be collected by the centre's principal investigator through the data collection dossier.

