### Data analysis

3.11

The research team will have a common space through a web platform to create and manage data. In this platform, a database will be generated for each centre to which only the researchers of each centre and the methodological team will have access. Also, a common database will be generated for all the centres to which only the project coordinator and the members of the methodological team will have access. The researchers of each centre will register the data in the specific database of each centre and will send the results in parallel to the study coordinator, who, through the methodological team, will also register the data in the common database. This will ensure the double entry of the data.

Descriptive statistics will be used to describe the sociodemographic and clinical characteristics of the patients through means and standard deviations (SD); frequencies and proportions. The chi‐square test (χ^2^) and the t‐test for independent samples will be used to detect any significant differences between the intervention and control groups on baseline variables. A repeated measures analysis of variance will be performed to analyse the relationship of the intervention with each of the dependent variables by introducing sociodemographic and clinical characteristics into the model.

To evaluate the effectiveness of the intervention, a multivariate analysis of covariance analysis (MANCOVA) will be performed, introducing the pretest‐posttest differences in the quality of the therapeutic relationship, the quality of psychiatric care and the perception of coercion as dependent variables. Statistical analyses will be performed using SPSS v27.

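### The CES-18 is described with two different objects and has no baseline, yet the joint MANCOVA makes the WAI-S and QPC results depend on it

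*Protocol article*

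**What the plan says.** Section 3.9 (Outcome measures) gives two descriptions of the CES-18. The first is general: "This scale assesses the subjective experience of coercion during psychiatric hospitalization". The second is tied to an event: "participants rate and record their own evaluation and self‐perception of the coercive intervention experienced". The scale has 18 items with five response options, anchored "1‐never and 5‐always".

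Section 3.10 (Recruitment and data collection) says that the T1 dossier "will consist of administering the WAI‐S and QPQ instruments" (the second acronym is evidently the QPC). The CES appears only at discharge, in "the follow‐up assessment included in the T2 dossier, which will include the WAI‐S, the QPC and the CES (T2". It is given without any condition on what happened during the stay.

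Section 3.5 requires no coercive measure for entry and excludes patients under mechanical restraint at recruitment. The Background describes Spanish units as places "where some users are admitted involuntarily" and gives no proportion.

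Section 3.11 (Data analysis) plans a repeated-measures analysis of variance for each dependent variable. It then says that, to evaluate effectiveness, "a multivariate analysis of covariance analysis (MANCOVA) will be performed", with pre-post differences in therapeutic relationship, quality of care and perceived coercion as joint dependent variables.

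**The concern.** Two features of the plan interact.

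First, the event-based description leaves unclear what a patient who had no coercive measure should do with the scale. Such patients are foreseeable under the entry criteria, and some may find the wording inapplicable and leave the form blank.

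Second, a MANCOVA in its standard form uses only patients with every dependent variable present. Placing coercion beside WAI-S and QPC makes the evaluation of the main outcome depend on completeness of a secondary scale. Coercive measures during the stay occur after the units are randomised, and Hypothesis 3 expects the intervention to lower perceived coercion. If answering the CES depended on having been coerced, the analysed subset could therefore differ between arms.

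The absence of a baseline CES makes the joint model more fragile still, because one of its three dependent variables is a difference with no first term.

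**Working it through.** **Step 1. Which CES quantity can be formed.**

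| Scale | T1 (3.10) | T2 (3.10) | Pre-post difference needed by 3.11 |
|---|---|---|---|
| WAI-S | yes | yes | can be formed |
| QPC | yes | yes | can be formed |
| CES | no | yes | cannot be formed for any participant |

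Read literally, the joint model has no complete cases. It can be fitted only if something else, most naturally the T2 CES score, replaces the difference. Steps 3 and 4 assume that substitution.

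**Step 2. Reproduce the planned sample size.** Inputs from section 3.6: difference 3, SD 10, pre-post correlation 0.7, two-sided alpha 0.05, power 0.80, loss to follow-up 20%.

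- SD of change = 10 × √(2 × (1 − 0.7)) = 7.746
- n per group = 2 × (7.746 × (1.960 + 0.842) / 3)² = 104.65, so 105 completers
- With losses: 104.65 / 0.8 = 130.8, the stated 131 (132 if 105 is rounded first)

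The planned figure is reproduced and is not in dispute. It uses a pre-post correlation, so it does not size the CES comparison.

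**Step 3. Effect of blank CES forms on the WAI-S within the joint model.** Let f be the share of completers without a CES value. The documents give no value, so f is assumed and shown as a range. Evaluable n per group = 105 × (1 − f). Power = Φ(3 / (7.746 × √(2/n)) − 1.960).

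For f = 20%: n = 84; 7.746 × √(2/84) = 1.195; 3 / 1.195 = 2.510; Φ(0.550) = 0.709.

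| Assumed f | n per group | Power for 3 units |
|---|---|---|
| 0% | 105 | 80.1% |
| 10% | 94.5 | 75.9% |
| 20% | 84 | 70.9% |
| 30% | 73.5 | 65.1% |
| 50% | 52.5 | 51.0% |
| 70% | 31.5 | 33.6% |

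A t-based calculation gives 79.8% at 105 and 70.4% at 84, so the method makes little difference. The figures treat patients as independent, ignore clustering by unit, and use a univariate test as a stand-in for the WAI-S part of the multivariate one.

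**Step 4. The other possible response.** If patients without a coercive measure answer in the lowest category throughout, f = 0 and no WAI-S or QPC data are lost. The CES would then collect scores at its minimum: 18 × 1 = 18 on a range up to 18 × 5 = 90, if items are summed (the scoring is not stated). That affects the shape of the CES distribution and leaves the WAI-S analysis untouched.

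**The case against.** The strongest reply is that the event-based clause is only loose wording. Section 3.9 first defines the scale as coercion during hospitalisation, and section 3.1 sets the objective as coercion perceived by hospitalised people. Neither requires a formal measure. The lowest response category is a valid answer, and a nurse trained in the instruments administers the scale. Voluntary admission is also not the same as absence of coercion: the Background says that most units are locked, and the Discussion says that many patients feel their rights are violated. All of this stands. A reader might infer that patients without a coercive intervention have nothing to rate, or that the effectiveness analysis shrinks to coerced patients. The documents support neither inference.

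It can also be said that missing-data rules may sit in an analysis plan that is not shown, that any blank rate is assumed, and that the WAI-S has its own repeated-measures analysis, which a blank CES does not affect. These points also stand, and they limit the size of the problem. They do not remove it, because section 3.11 itself assigns the evaluation of effectiveness to the joint model. No missing-data rule resolves the two descriptions of the scale, and none supplies a T1 CES that section 3.10 does not collect.

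**Conclusion.** The point holds in a limited form. The article gives the CES-18 two objects, gives it to everyone at T2 only, and ties WAI-S and QPC to it in the model named for effectiveness. The part that needs no assumption is that the CES pre-post difference does not exist for any participant.

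The loss of WAI-S power is conditional on T2 CES replacing that difference and on an unknown blank rate. It runs from none, through about 10 percentage points at 20% blank, to larger losses at higher rates. It applies only to the joint model and leaves the separate WAI-S analysis intact.

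A reader might also infer that a floor in the CES makes a comparison of means invalid. Nothing in the documents shows this. It is a reason for a sensitivity analysis and does not by itself require replacing the mean difference in Hypothesis 3.

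**What to change.** - **Section 3.11:** take the CES out of the joint model, so that WAI-S and QPC are analysed in all patients who have those scales, whatever their CES status.
- **Section 3.11:** compare T2 CES between arms in all participants as a separate secondary analysis, and describe it as a T2 comparison, not a change. Add a method that tolerates a floor (for example rank-based or proportional-odds) as a sensitivity analysis.
- **Section 3.9:** state one object for the CES-18, namely coercion perceived during the stay. Patients without a formal measure then answer the items themselves. They should not be assigned the minimum of 18, which could override real answers on humiliation or fear.

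The cost is wording only, with no extra patients, visits or instruments. The small downside is that there is no longer a single joint test across the three outcomes.

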### Recruitment and data collection

3.10

Once the centres have been randomized and the collaborating nurses of the units where the intervention will be carried out have been trained, the person from the research team coordinating the study in each unit will be responsible for informing the patients who meet the inclusion criteria between 24 and 72 h from the time of admission about the objectives of the study and will obtain informed consent. Patients will be recruited consecutively and will receive a confidential code assigned by the project coordinator, which will be their identification for the data collection dossiers. In the case of patients from centres chosen for the intervention, one of the nurses who has received the training will be assigned to the patient. In the case of control centres, the usual process of assigning a nurse from the unit will be followed and the nurse will not have any notification in this regard. In both cases, once the first meeting or welcome interview by the referring nurse in the unit has taken place, the baseline assessment (T1) will be carried out by a nurse who is not involved in the patient's care process and who has been previously trained in the measurement instruments. The baseline assessment will be included in the T1 dossier and will consist of administering the WAI‐S and QPQ instruments. Prior to discharge, the same person outside the care process of the hospitalized person will administer the instruments to the user for the follow‐up assessment included in the T2 dossier, which will include the WAI‐S, the QPC and the CES (T2). The remaining data will be obtained from the patient's clinical history and will be collected by the centre's principal investigator through the data collection dossier.

### Data analysis

3.11

The research team will have a common space through a web platform to create and manage data. In this platform, a database will be generated for each centre to which only the researchers of each centre and the methodological team will have access. Also, a common database will be generated for all the centres to which only the project coordinator and the members of the methodological team will have access. The researchers of each centre will register the data in the specific database of each centre and will send the results in parallel to the study coordinator, who, through the methodological team, will also register the data in the common database. This will ensure the double entry of the data.

Descriptive statistics will be used to describe the sociodemographic and clinical characteristics of the patients through means and standard deviations (SD); frequencies and proportions. The chi‐square test (χ^2^) and the t‐test for independent samples will be used to detect any significant differences between the intervention and control groups on baseline variables. A repeated measures analysis of variance will be performed to analyse the relationship of the intervention with each of the dependent variables by introducing sociodemographic and clinical characteristics into the model.

To evaluate the effectiveness of the intervention, a multivariate analysis of covariance analysis (MANCOVA) will be performed, introducing the pretest‐posttest differences in the quality of the therapeutic relationship, the quality of psychiatric care and the perception of coercion as dependent variables. Statistical analyses will be performed using SPSS v27.

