### Study setting and population

3.4

The study population will be patients hospitalized in acute mental health units in Spain. A total of 12 mental health hospitalization units will participate. The mental health units have been invited through the Spanish Association of Mental Health Nursing following territorial criteria of representativeness by autonomous community.

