### Sample size

3.6

Accepting an alpha risk of 0.05 and a beta risk of 0.2 in a bilateral contrast, 131 subjects in the first group and 131 in the second group are required to detect a difference equal to or greater than 3 units. The common standard deviation is assumed to be 10 with a correlation coefficient between the initial and final measurement of 0.7. A loss‐to‐follow‐up rate of 20% was estimated.

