### Randomization

3.7

Given the difficulties due to the evaluation conditions in real clinical practice for a traditional randomization of the subjects or a randomization by clusters, and bearing in mind that not all the nurses in the units will participate in the intervention, the units will be paired by similarity of structural characteristics in terms of number of beds and will be randomized through a computer program to an intervention or control group. Randomization will take place prior to the training of the nurses and the recruitment of the subjects. The intervention will be blinded at the subject level.

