### Strengths and limitations

4.1

This study has several limitations. The first limitation is the impossibility of randomizing the subjects to the groups due to pragmatic factors in the real clinical practice condition. Therefore, we decided to pair centres with similar characteristics and subsequently randomize each centre to the intervention or control group.

Another possible limitation is that the evaluator will know which group each centre belongs to, for this reason, we have decided to train these evaluators beforehand so that they collect the information in the same manner, and it is also foreseen that these evaluators will be external to the research team.

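### Whole units are randomised in pairs, but the named analyses take the patient as the independent unit; any positive within-unit correlation makes p-values too small and intervals too narrow

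*Protocol article*

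**What the plan says.** Allocation is by unit. Study setting and population (3.4): "A total of 12 mental health hospitalization units will participate". Randomization (3.7): "the units will be paired by similarity of structural characteristics in terms of number of beds and will be randomized through a computer program". Strengths and limitations (4.1) repeats it: "we decided to pair centres with similar characteristics and subsequently randomize each centre to the intervention or control group". Every patient recruited in a unit therefore has the same allocation, and pairing implies 6 units per arm. Section 3.7 cites difficulties with cluster randomisation as a reason for this scheme, yet the scheme is a matched-pair cluster randomisation.

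The analysis is in Data analysis (3.11). Baseline comparisons use chi-square and independent-samples t-tests. Then "A repeated measures analysis of variance will be performed to analyse the relationship of the intervention with each of the dependent variables", with sociodemographic and clinical characteristics added. For effectiveness, "a multivariate analysis of covariance analysis (MANCOVA) will be performed" on the pre-post differences in the three outcomes. No unit, pair or nurse term is named, and no mixed model, cluster-robust variance or unit-level analysis.

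Sample size (3.6): "131 subjects in the first group and 131 in the second group are required". The target is a 3-point difference at two-sided alpha 0.05 with 80% power. The assumed SD is 10, the pre-post correlation 0.7 and the loss to follow-up 20%. No ICC or design effect appears.

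**The concern.** Patients in one unit share nurses, staffing and ward rules, and the Background itself lists such ward-level factors as influences on the therapeutic relationship. When units are allocated, variation between units is part of the error of the group comparison. A repeated-measures ANOVA or MANCOVA with patients as the independent units leaves that part out. It works with about 2 × 105 − 2 = 208 error degrees of freedom, whereas the design supplies 12 − 2 = 10, or 6 − 1 = 5 if the pairs are kept.

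At stake is the main claim of the trial. A significant result could reflect which wards were drawn into which arm, and the reported interval would not show that uncertainty.

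**Working it through.** **1. The plan's own sample size.** Inputs from section 3.6: difference 3, SD 10, correlation 0.7, two-sided alpha 0.05, power 80%, loss 20%.

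- SD of the change score: 10 × √(2 × (1 − 0.7)) = 7.746.
- Per arm: 2 × [7.746 × (1.960 + 0.842) / 3]² = 104.65, so 105 evaluable.
- With losses: 104.65 / 0.8 = 130.8, so 131.

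The stated figure reproduces with a design effect of 1. The sizing therefore treats patients as independent, in line with the analyses named in 3.11.

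**2. Understatement of the standard error.** 105 evaluable patients in 6 units per arm give m = 105 / 6 = 17.5 per unit. The ICC of the analysed score is an assumption, shown as a range.

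- Matching explains nothing: variance ratio D = 1 + (m − 1) × ICC = 1 + 16.5 × ICC.
- Pairs carry half the between-unit variance (assumption): that half cancels in the group difference, so D = 1 + (m/2 − 1) × ICC = 1 + 7.75 × ICC.
- True type I error of a nominal 5% patient-level test: 2 × P(Z > 1.96 / √D).

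| ICC | D, no pair effect | True/naive SE (√D) | Type I error | D, pairs carry half | Type I error |
|---|---|---|---|---|---|
| 0.01 | 1.17 | 1.08 | 6.9% | 1.08 | 5.9% |
| 0.02 | 1.33 | 1.15 | 8.9% | 1.16 | 6.8% |
| 0.05 | 1.83 | 1.35 | 14.7% | 1.39 | 9.6% |
| 0.10 | 2.65 | 1.63 | 22.9% | 1.78 | 14.1% |

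**3. Simulation.** 20,000 null trials per setting, 12 units × 17 patients, one outcome.

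- No pair effect: the patient-level t-test rejected 7.2 / 9.1 / 14.8 / 22.5% at the four ICCs, and 5.2% at ICC 0. The unpaired t-test on the 12 unit means stayed at about 5%.
- Pairs carry half: the patient-level test rejected 5.7 / 6.9 / 9.6 / 14.0%. The unpaired unit-mean test became conservative (4.3 / 3.8 / 2.8 / 2.3%), while the paired one held 5%.

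**4. Width and power of a valid analysis** (105 evaluable per arm, 10 df, no pair effect).

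- Interval width relative to the naive one: √D × 2.228 / 1.96 = 1.23 / 1.31 / 1.54 / 1.85.
- Standard error on the change score: 7.746 × √(2/105) × √D = 1.069 × √D.
- Non-centrality 3 / SE = 2.60 / 2.43 / 2.08 / 1.72, so power is about 65 / 59 / 47 / 34%.
- With T2 adjusted for T1 the SD becomes 10 × √(1 − 0.7²) = 7.14. At the same ICCs power is then about 72 / 66 / 53 / 39%, still below 80%.

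**The case against.** **The full analysis plan is not shown.** Section 3.11 lists covariates for the ANOVA only; for the MANCOVA it lists none. A reader might infer that unit is definitely excluded. The text supports only that no unit or pair term is named. Even so, the article fixes the methods, the dependent variables and the kind of covariates, and the sample size rests on the same independence. This is more than silence.

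**Change scores remove stable ward differences.** This is partly right. The Background factors bear mainly on score levels, and only unit-level variation in change matters for a difference score. The ICC of change could be small, and values of 0.05 to 0.10 have no support in the document. Differencing does not remove unit variation in change, however, and it does not help the coercion scale, which section 3.10 lists at T2 only.

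**Matching on beds may help.** It may, which is why the second set of figures is given. Some inflation remains at every positive ICC unless the pairs carry nearly all the between-unit variance.

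**The figures are not the error rate of the main test.** A reader might take the 7 to 23% as the error rate of the MANCOVA. It is not; it belongs to a single-outcome patient-level test. A three-outcome multivariate test, simulated with an assumed outcome correlation of 0.4, the same ICC for all outcomes and no pair effect, rejected about 8 / 11 / 23 / 39%. That depends on further assumptions and is only indicative, but it does not favour the plan.

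**Conclusion.** The point stands in conditional form. The unit is randomised, the named analyses take the patient as independent, and for any positive within-unit correlation of the analysed score the standard error is understated. The direction follows from the design; the size rests on an ICC that the protocol does not give. Over 0.01 to 0.10, with about 17 completers per unit, the true error of a single-outcome test is about 7 to 23% without a pair effect and about 6 to 14% if pairs carry half the between-unit variance.

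An unconditional claim that the p-values are wrong would go too far: at an ICC of zero the patient-level test holds its level. This should be corrected before analysis, because it affects the main conclusion and the analysis can be changed without new patient data.

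**What to change.** In section 3.11, for each outcome:

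- Analyse the T2 score adjusted for its T1 score, in a linear mixed model with group as fixed effect, a random intercept for unit, and Kenward-Roger or Satterthwaite degrees of freedom. The coercion scale, listed only at T2, goes in without a T1 term. State the response explicitly: if both time points were modelled together, a unit intercept alone would not capture unit variation in change.
- Account for the randomisation pair, or state in advance that the matching is broken.
- Add a check on the 12 unit means, paired if pairs are kept; the unpaired version is conservative when the matching works.
- A nurse-within-unit term is optional, and possible only if nurse identity is recorded. The text does not say that it is; the centre is identifiable from the per-centre databases.

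A multivariate test is not itself the fault; if one is kept, it too needs the unit level.

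Cost: no new patient data. Intervals widen, and power falls below the stated 80% (about 65 / 59 / 47 / 34% for change scores on 10 df at the four ICCs). Section 3.6 should therefore restate the power with a stated ICC.

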### Ethical considerations

3.12

This project has received approval by the bioethics committee of the ‘REDACTED’ and by each of the reference ethics committees for each of the other participating institutions. The consequent authorization will be requested from all participants for the public result that will be given to the data, preserving anonymity and strict confidentiality at all times, and therefore the name of the participants will be coded and numbered. The data obtained will be incorporated into an electronic database and the information provided will be treated as completely confidential. Any data or name that might reveal the identity of the informants will be eliminated. The persons who participate will do so voluntarily, signing the corresponding consent of acceptance of the study conditions, with the right to withdraw from the study at all times.

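### As written, the joint MANCOVA on three change scores uses only patients with every difference observed; CES has no baseline, so no patient qualifies, and WAI-S should be analysed on its own

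*Protocol article*

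**What the plan says.** All places are in the protocol article.

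- **3.11 Data analysis** names two models. Effectiveness is tested by one MANCOVA, "introducing the pretest‐posttest differences in the quality of the therapeutic relationship, the quality of psychiatric care and the perception of coercion as dependent variables". A repeated measures ANOVA with sociodemographic and clinical covariates is also run, once per outcome. The MANCOVA covariates are not listed.
- **3.10 Recruitment and data collection** fixes the two assessments. The T1 dossier "will consist of administering the WAI‐S and QPQ instruments" (QPQ is evidently the QPC). T2 is collected once: "Prior to discharge, the same person outside the care process of the hospitalized person will administer the instruments to the user for the follow‐up assessment". CES appears only in the T2 dossier.
- **3.6 Sample size** states: "A loss‐to‐follow‐up rate of 20% was estimated".
- **3.12 Ethical considerations** lets patients take part "with the right to withdraw from the study at all times".

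The article does not say how a missing T2 or a missing scale is handled.

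**The concern.** A patient who leaves or withdraws before the T2 assessment has no pretest-posttest difference on any scale. A MANCOVA needs every dependent variable for every patient it uses, so a valid WAI-S pair is also discarded when the QPC or CES difference is missing. Tying the primary outcome to two other scales in this way gains nothing for the main hypothesis.

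Two things are at stake. First, the model may not be computable on the document's own assessment schedule. Second, early departure may be related to the nurse-patient relationship, which is the outcome, and the intervention aims to change that relationship. If loss differs between arms and is related to the score, a comparison of completers' change scores can be biased. Enlarging the sample for expected loss restores precision but does not remove such bias.

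**Working it through.** **1. The plan's own figure.** Section 3.6 gives a two-sided alpha of 0.05, power of 0.80, a target difference of 3 and 131 patients per arm. Its variance assumption reads: "The common standard deviation is assumed to be 10 with a correlation coefficient between the initial and final measurement of 0.7".

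- SD of the change score = 10 × √(2 × (1 − 0.7)) = √60 = 7.746.
- n per group = 2 × 60 × (1.960 + 0.842)² / 3² = 104.65.
- Allowing for 20% loss: 104.65 / 0.8 = 130.8, so 131.

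The 131 is reproduced. It already contains the expected loss: about 26 of 131 per group without T2, about 105 pairs remaining, and about 80% power on the change score.

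**2. Who enters each model, if nothing is imputed.**

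| Outcome | T1 | T2 | Difference exists? | Per-outcome repeated measures ANOVA |
|---|---|---|---|---|
| WAI-S | yes | yes | if T2 done | patients with both visits |
| QPC | yes | yes | if T2 done | patients with both visits |
| CES | no | yes | for nobody | cannot be run |

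The joint MANCOVA needs all three differences. Because the CES difference exists for nobody, it has no complete case.

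**3. Cost of listwise deletion if the CES problem were resolved.** The documents give no rate of scale-specific missingness, so the rates here are assumptions. If a further 5%, 10% or 20% of assessed patients lacked at least one difference, 131 × 0.8 × 0.95, 0.90 or 0.80 leaves about 100, 94 or 84 per group. Change-score power (normal approximation, before any clustering by unit) is then 78.0%, 75.8% or 70.8%. One assessor gives all scales in one T2 dossier, so the lower end is the more natural case.

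**4. Possible bias in completers' change scores.** Assumptions: T1 and T2 are bivariate normal with the plan's SD 10, correlation 0.7 and true effect 3. Loss follows a probit model whose latent variable has correlation r = 0.3 to 0.7 with T1, low scorers being lost more often. Average loss is 20%.

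- Among completers the T1 mean rises by 10 × r × m(p), where p is the proportion lost and m(p) = φ(z_p)/(1 − p).
- Since T2 regresses on T1 with slope 0.7, the mean change shifts by −0.3 × 10 × r × m(p) = −3r × m(p).
- Bias in the arm contrast = 3r × (m(control) − m(RTS)).

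| Loss, control / RTS | m(control) − m(RTS) | Estimate, r = 0.3 to 0.7 |
|---|---|---|
| 20% / 20% | 0 | 3.00 |
| 25% / 15% | 0.4237 − 0.2743 = 0.1494 | 3.13 to 3.31 |
| 30% / 10% | 0.4967 − 0.1950 = 0.3017 | 3.27 to 3.63 |

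Simulation agrees (3.12 to 3.64 across the unequal splits). The overstatement is about 0.1 to 0.6 points, against a standard error of √(2 × 60/105) = 1.07. In the same simulations an analysis conditioning on T1 returns 2.98 to 3.01.

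**5. Loss that depends on the unseen T2 score.** With the same unequal splits, estimates fall to between 1.8 and 2.9. Conditioning on T1 does not repair this. At 30% / 10% and r = 0.7 the change score gives 2.37 and the T1-adjusted contrast 1.81.

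**The case against.** The strongest reply is that this is an unwritten missing-data policy, which a journal article may properly leave to the full protocol or analysis plan. That stands in part. A reader might infer from 3.11 that patients without T2 can only be dropped. The document does not support that: it does not state a complete-case analysis, and imputation before the MANCOVA is not ruled out. What the article does fix is the model, its dependent variables and the assessment schedule, and those can be judged.

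Four further objections limit the point, and each stands:

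- A reader might infer that one blank scale removes a patient from both analyses. It does so only in the joint MANCOVA; the repeated measures ANOVA is run per outcome.
- A reader might infer that the expected 20% loss erodes power. It does not, because the 131 already allows for it.
- A reader might take the bias as shown. It rests wholly on assumed loss patterns. No document gives loss by arm or its dependence on the score, the right to withdraw is ordinary consent wording, and equal loss gives no bias.
- In the T1-dependent scenario the bias comes from not conditioning on T1, not from dropping patients as such: a completers' analysis with T1 as covariate also returns about 3. T1 may be among the unlisted MANCOVA covariates.

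None of this rescues the joint model, which lacks a CES difference for every patient.

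**Conclusion.** The point holds in a limited form. As written, the effectiveness analysis is a joint model that uses only patients with all three differences, and on the schedule in 3.10 no patient has all three. That part rests on the document alone: sections 3.10 and 3.11 contradict each other and must be reconciled.

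The bias is a risk and not a demonstrated error. It is about 0.1 to 0.6 points on an effect of 3 (4% to 21%) under the assumed unequal, T1-dependent loss, and nil under equal loss. The upper end needs three times as much loss in the control arm and a latent correlation of 0.7. A better method is available at little cost, so the change should be made, but confidence in the size of the benefit is only moderate.

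**What to change.** In 3.11, replace the joint MANCOVA with a separate analysis for each outcome.

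- **WAI-S (primary) and QPC:** a linear mixed model on the T1 and T2 scores that keeps every patient with a T1 score, in the group to which their unit was randomised. At the least, include T1 as a covariate. A WAI-S pair must not depend on QPC or CES being present.
- **CES:** compare T2 scores only, and make 3.10 and 3.11 agree. The T1/T2 model cannot be fitted to this scale.
- **Reporting:** give T2 loss by arm and by reason.
- **Sensitivity:** repeat the WAI-S analysis with unobserved T2 scores shifted downward in one arm at a time, for example by 3 and 6 units (one and two times the planned difference; the values are illustrative).

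The cost is changed wording and a little more analysis work. The mixed model can be fitted in SPSS, which the plan already names, and no new patients, visits or data are needed. The small downside is that the model assumes loss is explained by the recorded data; the sensitivity analysis is there to test that.
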